#### Sample size estimation and statistical analyses

To elucidate a difference in physical performance between the intervention and the control groups, we used data from previous studies (average ± standard deviation of the TUG score in patients discharged home after post-surgery rehabilitation of 13 ± 3.5 s and TUG minimal detectable change of 2.5 s) [16, 17] to determine the required sample size. Twenty-five participants per group will provide adequate power to detect statistically significant differences in the TUG score between the two groups (allocation ratio 1; statistical power 80%; alpha level 0.05), but 56 patients will be recruited in total anticipating a dropout rate of 10%.

The statistical analysis of the results will be performed by a blinded expert. The Kolmogorov-Smirnov test will be adopted to check the normality of data distribution. Within- and between-group comparisons will be performed by a two-sample *t* test or one-way and two-way ANOVA.

The extent of missing data will be explored in the outcomes, especially the primary outcome. Patterns of missing data will be explored and predictors of missingness examined, especially if these vary by intervention. If necessary, multiple imputation will be used to impute missing data assuming the missingness mechanism is missing at random. A detailed statistical analysis plan will be agreed to before the end of data entry and before the treatment code is broken.

Data will be expressed as mean ± standard deviation (normally distributed data) or median and interquartile range (non-normally distributed data). The threshold for statistical significance will be set to *P* = 0.05. All statistical tests will be performed with MATLAB (The MathWorks, Inc., Natick, MA, USA) software package.

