The usual rehabilitation settings and care path after THA in Italy consist of a short (2–3 weeks) stay in a rehabilitation clinic followed by home-based rehabilitation. The unsupervised execution of a home-based rehabilitation program implies that patients are individually charged with the responsibility to undertake exercises at a time and a place convenient to their needs and daily living schedules. However, low personal motivation and misunderstanding the instructions to execute the program can negatively affect the outcome of individual rehabilitation programs. Therefore, it has been suggested that patient supervision may be a key factor to achieve the best possible rehabilitation results in some populations [11].

We hypothesized that a home-based telerehabilitation program performed through the remote supervision of the patient’s performance and adherence can improve clinical outcomes compared to conventional (unsupervised) home-based care.

Therefore, the overall objective of this study is to evaluate the effectiveness of a new telerehabilitation solution, ReHub, for the physical function and clinical outcome improvement following THA. The specific aims of this manuscript are to describe the study design, protocol, content of interventions, and primary and secondary outcomes and to discuss the clinical rehabilitation impact of the expected experimental results.

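### Twenty-five per group gives 80% power only with an undeclared one-sided test; for a two-sided comparison the power is about 70%

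*Protocol article*

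**What the plan says.** The protocol article, under Sample size estimation and statistical analyses, gives a TUG mean of 13 s with standard deviation 3.5 s, taken from earlier studies, and a "TUG minimal detectable change of 2.5 s". The design settings are "allocation ratio 1; statistical power 80%; alpha level 0.05". From these it concludes: "Twenty-five participants per group will provide adequate power to detect statistically significant differences in the TUG score between the two groups". Recruitment is then raised to 56 in total to allow for 10% dropout.

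On the analysis, the same section says: "Within- and between-group comparisons will be performed by a two-sample" t test or by one-way and two-way ANOVA. It adds: "The threshold for statistical significance will be set to" P = 0.05. Neither the sample-size text nor the analysis text says whether the tests are one- or two-sided. No correlation between visits and no baseline adjustment enters the calculation.

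The Background gives the hypothesis a direction: remotely supervised home rehabilitation "can improve clinical outcomes compared to conventional (unsupervised) home-based care".

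**The concern.** All the inputs to a standard two-group calculation are given, so the figure of 25 can be checked. Under the usual reading of alpha 0.05 as two-sided, 25 looks too small for a standardised difference of about 0.71.

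Two things are at stake. First, TUG is the sole primary outcome. If the result is null, readers will judge it against 80% power, when a true 2.5 s benefit would be missed about three times in ten. Second, undeclared sidedness leaves a choice open until the data are seen. A result in the hoped-for direction with a two-sided p-value between 0.05 and 0.10 would be significant one-sided and not significant two-sided.

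**Working it through.** **Inputs** (all from the sample-size paragraph): difference Δ = 2.5 s; SD σ = 3.5 s; α = 0.05; power 80%; allocation 1:1; 25 per group; 10% dropout; 56 recruited.

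Standardised difference: d = 2.5/3.5 = 0.714, so d² = 0.510.

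**Step 1. Reproduce the stated figure.** The normal-approximation formula is n per group = 2(z_α + z_β)²/d², with z_β = 0.842 for 80% power.

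- One-sided α = 0.05: 2(1.645 + 0.842)²/0.510 = 24.2, rounded up to **25**. This is the stated figure.
- Two-sided α = 0.05: 2(1.960 + 0.842)²/0.510 = 30.8, rounded up to **31**.

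The dropout step is correct: 50/0.9 = 55.6, rounded up to 56.

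**Step 2. Exact check.** For the two-sample t test, power comes from the noncentral t distribution with 2n − 2 degrees of freedom and noncentrality d√(n/2). At n = 25 the noncentrality is 0.714 × √12.5 = 2.525.

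| Completers per group | One-sided 0.05 | Two-sided 0.05 |
|---|---|---|
| 25 | 80.1% | **69.7%** |
| 28 (no dropout) | 84.0% | 74.7% |
| 31 | – | 79.0% |
| 32 | – | 80.3% |

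The normal approximation at 25 per group agrees closely: Φ(2.525 − 1.645) = 81.1% one-sided and Φ(2.525 − 1.960) = 71.4% two-sided.

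The two-sided requirement is therefore 32 per group, or 64 completers. Allowing for dropout, 64/0.9 = 71.1, which is 72 recruited.

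**Step 3. Could another two-sided route give 25?** These variants were tried for 80% power:

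- Inflation for a rank test: 34 to 37 per group.
- A one-sample or paired formula: 18.
- Unrounded values of Δ (2.45 to 2.54 s) and σ (3.45 to 3.5 s): 30 to 34 per group.

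None gives 25.

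**Step 4. What 25 per group would need for 80% two-sided power.** Any one of these would do:

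- A true difference of 2.83 s instead of 2.5 s.
- An SD of 3.09 s instead of 3.5 s.
- Adjustment for baseline TUG, which multiplies the SD by √(1 − ρ²). The condition is √(1 − ρ²) = 3.09/3.5 = 0.883, so ρ is about 0.47.
- A change-score analysis, which multiplies the SD by √(2(1 − ρ)). The condition is 2(1 − ρ) = 0.883² = 0.780, so ρ is about 0.61.

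The article states none of these.

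**The case against.** The strongest reply is that the article never calls its tests two-sided, and its hypothesis is directional. Read as one-sided, the calculation is correct: 25 per group gives 80.1%. The ANOVA argument is also not conclusive. The t test and ANOVA are listed together for all within- and between-group comparisons, and ANOVA is not assigned to the primary comparison. A t test can be run one-sided. A detailed analysis plan was still to be agreed and might settle the matter.

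Part of this stands. Two-sidedness is inferred from the text, not stated in it, and a one-sided test may have been what the authors had in mind. But a directional hypothesis does not make a test one-sided. A reader who meets alpha 0.05, P = 0.05 and a search for differences, with no direction declared, will take the test as two-sided. For two groups, one-way ANOVA is identical to the two-sided t test, so at least one of the named methods cannot deliver the stated power on these inputs. A later analysis plan can define the test, but it cannot make the published power right for a two-sided comparison.

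It is also fair to say that the shortfall is moderate, about 10 percentage points. Under a two-sided test it neither biases the estimate nor inflates the type I error. That limits the harm but leaves the stated figure wrong.

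**Conclusion.** The concern holds. With the article's own inputs and an unadjusted comparison of two groups, 25 per group corresponds to one-sided alpha 0.05. The two-sided power is 69.7% with the expected dropout and 74.7% with none, against the stated 80%. The shortfall in sample size is 7 completers per group (32 against 25), too large to be rounding or a choice between normal and t formulas.

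This rests on three assumptions: the primary test is two-sided at 0.05, which is the natural reading of the text; the SD of 3.5 s applies in both groups at the time of comparison; and no baseline adjustment is used. If a one-sided test was intended, the arithmetic is right and the fault is that the test was not declared. The paragraph needs correcting in either case.

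**What to change.** **Preferred change.** In the sample-size paragraph, declare all tests two-sided. State that 25 completers per group give about 70% power for a difference of 2.5 s with SD 3.5 s, or 80% power for 2.83 s. This costs wording and a less favourable power figure, and needs no extra patients.

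**Recovering 80% without more patients.** Specify the primary analysis as TUG at the final visit (t3) adjusted for TUG at admission (t1), and state the assumed correlation. It must be at least about 0.47. The article gives no such correlation, so recovery cannot be taken for granted. TUG at discharge (t2) is a less safe covariate, because the groups already receive different familiarisation sessions during the inpatient stay.

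**Keeping 80% power unadjusted.** Recruit 72 instead of 56, that is 16 more patients.

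**If a one-sided test was intended.** Declare and justify it, and name a directional test for the primary comparison in place of ANOVA. Readers should be told that this is the same threshold as a two-sided 10% level in the favourable direction.

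Whichever route is taken, fix it in the analysis plan before the treatment code is broken. By the article's own account, recruitment was continuing and that plan had still to be agreed.

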## Discussion

The study aims to assess the effectiveness of a home-based telerehabilitation program for the physical function and clinical outcome improvement following THA.

The randomized controlled design, blinding of the physician performing the outcome assessments, and use of valid tools for the assessment of physical performance and muscle strength (TUG score and dynamometer-based measurements of muscle strength under isometric conditions, respectively) are the notable strengths of the study.

Limitations of the study include the absence of specific investigations (e.g., electromyography, muscle ultrasonography) providing possible insights into the neural and muscular mechanisms underlying the effects of telerehabilitation in responder patients (or explaining the non-responder phenotype) and the lack of assessment of patient satisfaction and preferences providing possible insights into the treatment attributes considered most important by the patients [18].

Other study limitations are represented by the short intervention duration (3 weeks) and the lack of a long-term follow-up that could help determine whether the possible improvements in physical function induced by the telerehabilitation program may produce long-lasting benefits in physical performance and health.

Notwithstanding these limitations, demonstrating the effectiveness of a home-based telerehabilitation program for physical function and/or muscle strength improvement following THA could have relevant implications for the post-surgical rehabilitation process. In fact, telerehabilitation solutions can facilitate access and adherence to health interventions, reduce health care costs (associated with supervision, facility provision, and transport of patients), and contribute also to social distancing when it becomes necessary as an infection control action.

In addition, the direct and indirect costs of using the telerehabilitation system compared with the costs of the traditional rehabilitation programs commonly adopted in THA patients will also be assessed.

Therefore, proving the clinical and cost-effectiveness of a home-based telerehabilitation program for physical and muscle function following THA could support its systematic incorporation in post-surgical rehabilitation protocols, which should be tailored to the individual and collective needs.

Trial findings will be disseminated to the scientific community through publications and national and international conferences (authorship and time scales will be agreed by the Trial Management Group consisting of the trial manager, administrative staff, chief investigator, and statistician). Findings will also be disseminated to participants and patient organizations through social media and presentations at local conferences.

## Trial status

The Trial Management Group meets on a weekly basis to discuss progress and monitor recruitment, data returns, and so on.

The Trial Management Group meets also every 6 months for auditing trial conduct.

The first study participants were recruited into the trial in December 2019 (study protocol version 1, dated 20 September 2019). Patient recruitment and data collection are ongoing and will continue until the required number of study participants will be achieved (estimated date of the recruitment completion: November 2020).

## Abbreviations

FIM: Functional Independence Measure
GROC: Global rating of change
HOOS: Hip dysfunction and Osteoarthritis Outcome Scale
ROM: Range of motion
THA: Total hip arthroplasty
TUG: Timed Up-and-Go
